### Objectives

The *primary objective* of the study is to evaluate the validity of the model for pathological eating in elite sport [16]. The indicators (weight-sensitivity, weight- and shape pressure, internalisation of a sports discipline-specific body ideal, unhealthy training intentions and behaviour, fatigue) specified in the model are expected to explain variance in ED symptomatology (measured by EAT-26) and/or increase the likelihood of an ED (clinical interviews) in elite athletes. The *second aim* is to investigate whether the diagnostic accuracy of ED identification in elite sports can be improved by combining standardized instruments (e.g., EAT-26) with sport-specific indicators (e.g., ART). The goal is to empirically derive cut-off scores that prioritize high sensitivity to minimize the risk of false negatives, while maintaining acceptable levels of specificity. The *third aim* is to estimate the prevalence of EDs in elite athletes by both the number of diagnosed cases in this cohort and ED instruments. The prevalence in weight-sensitive sports disciplines is hypothesised to be higher compared to less weight-sensitive sport-disciplines and compared to a control group. *Further study objectives* are the identification of protective factors (e.g., sport type, nutrition knowledge) for DE, the investigation of the predictive validity of the indicators, and the association of physiological markers (e.g., body fat percentage) with DE in elite sports. Methodologically, this study aims at investigating whether conventional instruments measure ED symptoms differently in elite athletes than in the control group.

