### Study design and procedure

ENHANCE (Eating and Nutritional Habits in Athletes and Controls — a longitudinal Examination) is a prospective, non-interventional, longitudinal study combining quantitative assessments and semi-structured clinical interviews to evaluate the validity of our previously published theoretical model [16] and assess the prevalence of EDs among elite athletes, including a non-athlete control group for comparative analysis. At four assessment points (T0 – T3, see Fig. 1), sociodemographic, health, training, nutritional, and psychological data will be collected via digital assessments (created with Unipark software, Tivian XI GmbH) as self-reports from both the athlete and non-athlete group. Additionally, a subgroup of athletes will be invited to participate in clinical interviews and body measurements.

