**Fig. 1 Fig1:**
[figure not shown]
Flow chart of the study. Notes: T0: Baseline assessment, T1-T3: Time points for follow-up assessments, ED: Eating disorder, blinded: Regarding the scores of the index tests

After providing electronic informed consent, participants can access an eligibility screening by following the study link. Based on the eligibility screening, the participants are assigned to either the elite athletes or the control group, or will be excluded from the study (see section participant eligibility and recruitment). After completing the baseline assessment, controls can exit the survey, while elite athletes will be forwarded to an appointment booking system. There, they can optionally schedule an appointment for a clinical interview (online or in person, in German or English) and/or the body measurements approximately one month after baseline assessment. Trained specialists will conduct the clinical interviews and body measurements. Body measurements (i.e., body fat percentage) can also be conducted by an external health care professional chosen by the participant. Interview and body data are documented in an electronic case report file. Links to access the follow-up assessments are send via email by the study staff. All emails and reminders are standardized. Data of each assessment point will be linked using pseudonymized participant codes.

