### Participant eligibility and recruitment

All participants are required to speak and understand English fluently to be included in the study. This study is aimed at elite athletes who (a) practice either ballet, bodybuilding, racket sports, soccer, or basketball, (b) organise their daily life around their sport and (c) regularly participate in competitions or performances [1, 13, 36, 43, 44]. To be assigned to the elite athlete group, the training must have been practiced for at least six months with more than 300 min/week at moderate or higher intensity [36]. Participants, who fulfil the criteria for classification as elite athletes and practice one of the sports disciplines mentioned above, are included in the elite athletes group. Participants who do not meet the criteria of the elite athlete group are assigned to the control group. Participants in the control group may also train regularly but should not match the elite athletes’ criteria. If the participants fulfil the criteria to be considered elite athletes, but do not practice any of the sports disciplines examined in this study, they will be excluded from the study.

Participants are recruited purposefully at sports facilities, sports boarding-houses, ballet academies, ballet companies, sports clubs, fitness fairs, sports events, and on social media. Among other recruitment strategies, we search Instagram accounts affiliated with ball sport-, ballet-, or bodybuilding associations like the International Federation of Bodybuilding and Fitness. Moreover, ballet companies or academies are contacted to inform potential eligible participants about the study and distribute the recruitment material.

A screening prior to baseline assessment enrols eligible participants. They will be asked to provide their contact details in a survey link separate from study data, which is used to contact participants one, six and twelve months after baseline assessment for follow-up assessments (see Table 1.). Participation in the clinical interviews is voluntary for the athlete group.

**Table 1 Tab1:** Assessment Schedule

				Planned assessment time points								
				Athletes					Controls			
Criteria				T0	T1	T2	T3		T0	T1	T2	T3
	*Eating disorder (A) and Disordered eating (B)*											
			Clinical interviews		X							
			Eating Attitudes Test-26	X		X	X		X		X	X
			Eating Disorder Examination Questionnaire		X					X		
			Brief Eating Disorder in Athletes Questionnaire	X	X	X	X		X	X	X	X

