### Outcome measures

The primary outcome is the additional variance explanation in the psychopathology of eating behaviour in the elite sports group by the indicators (∆R²) of our theoretical model of DE [16]. The criteria of the regression models will be measured (A) binary conducting clinical interviews (ED present or absent) and (B) continuous using an ED instrument (severity of ED symptomatology).

*A)* Clinical interviews serve as a reference test. Trained specialists will assess participants for EDs (anorexia nervosa, bulimia nervosa, binge-eating disorder, and others) using ICD-11 criteria [14] in a ~ 30-minute interview. Based on the indicator internalization of a sport-specific body ideal, including muscular body images that can potentially contribute to EDs in elite sports, the criteria for muscle dysmorphia proposed by Pope et al. [45] are also part of the interview. ICD-11 criteria will be evaluated using selected questions of the ED examination interview from Lichtenstein et al. [26], allowing a sports-specific exploration of the fear of weight gain or behaviours to prevent weight gain, weight and shape concerns, food-related loss of control, exercise behaviour, and compensatory behaviours. Additionally, performance enhancing substance use, obsessive healthy eating, and physiological consequences of low energy availability in elite sports like reduced sex drive or menstrual dysfunction are evaluated [26, 46, 47]. In addition to the identification of EDs associated with clinically relevant psychosocial and physical impairments, borderline cases will be documented as DE presentations [48]. In comparison to the ICD-10, the ICD-11 might facilitate diagnosis in men by removing the endocrine disorder criterion [14]. Neither the interviewers nor the participants are informed about the results of the index tests.

*B)* The Eating Attitudes Test 26 [EAT-26; [49] evaluates the frequency of DE behaviours on a 6-point-scale with a cut-off of 12.66 indicating clinical risk in athletes [50, 51]. The EAT-26 is administered at T0, T2 and T3 and is used as a measure of ED symptom severity in the hierarchical regression analyses.

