Further, Receiver Operating Characteristic (ROC) curves and the AUC will be used to assess the diagnostic accuracy of individual and combined instruments to address the second aim. An AUC of 0.50 indicates no discriminative ability, values between 0.80 and 0.89 reflect good accuracy, and values between 0.90 and 1.00 indicate excellent accuracy. For each instrument or combinations of significant indicators from previous regression models, sensitivity (true positives / [true positives + false negatives]) and specificity (true negatives / [true negatives + false positives]), positive and negative likelihood will be calculated. To determine the optimal cut-off score for each instrument, Youden’s index [97] will be applied, identifying the point on the ROC curve that maximizes the sum of sensitivity and specificity (Youden’s J = Sensitivity + Specificity – 1). In addition, to minimize the risk of false negatives and thus the likelihood of overlooking athletes with clinically relevant eating pathology, alternative cut-off scores will also be evaluated by prioritizing a sensitivity of at least 80%, while maintaining an acceptable specificity threshold (e.g., ≥ 70%).

Significant predictors with the highest diagnostic accuracy will be included in logistic regression models as independent variables and ED diagnosis as dependent variable to calculate ORs. Based on this model, individual probabilities for the presence of an ED will be calculated for each participant in the athlete sample. The estimated prevalence is defined as the mean of these predicted probabilities. Mean differences of the probabilities (dependent variable) will be compared between the subgroups (independent variable) with ANOVAs for aim three. If the requirements for the analysis are not matched, we will conduct adequate alternative tests.

The *methodological examination* will be conducted by performing a measurement invariance using multi-group confirmatory factor analysis (CFA) to evaluate whether the factor structure of the ED instruments is equivalent between athletes and controls. ROC curves will be compared between athletes and controls, to assess if the identification of participants with or without an ED is better in controls than in athletes.

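### The athlete-versus-control ROC comparison has no reference standard in controls, and the control limb of aim 3 can rest only on self-report instruments

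*Protocol article*

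**What the plan says.** All references are to the protocol article.

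- **Reference standard.** Outcome measures, item A: "Clinical interviews serve as a reference test". It yields ED present or absent.
- **Who receives it.** Study design and procedure: "a subgroup of athletes will be invited to participate in clinical interviews and body measurements". The text under Fig. 1: "After completing the baseline assessment, controls can exit the survey, while elite athletes will be forwarded to an appointment booking system". Participant eligibility and recruitment: "Participation in the clinical interviews is voluntary for the athlete group". In Table 1 the interview row carries one mark, for athletes at T1. Sample size calculation assigns every planned interview to athletes.
- **Planned ROC comparison.** Planned data analysis, on the methodological examination: "ROC curves will be compared between athletes and controls, to assess if the identification of participants with or without an ED" is better in controls. This follows a multi-group CFA of the ED instruments across the two groups.
- **Aim 3.** Objectives: prevalence is to be estimated "by both the number of diagnosed cases in this cohort and ED instruments", and "The prevalence in weight-sensitive sports disciplines is hypothesised to be higher compared to less weight-sensitive sport-disciplines and compared to a control group". The only estimator described under Planned data analysis is the mean predicted probability from a logistic model of ED diagnosis: "individual probabilities for the presence of an ED will be calculated for each participant in the athlete sample".

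**The concern.** The ROC sentence describes an analysis that the study's own data collection cannot feed. This is not a detail that an article might leave to a fuller plan, because no analysis plan can supply interview results that are not collected.

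If the sentence stands, someone must choose a stand-in for ED status in controls after the data are in. Should athletes then be judged against an interview and controls against a questionnaire or a past diagnosis, the two AUCs would answer different questions. Their difference could be read as evidence that instruments work better or worse in athletes when it reflects only the change of reference.

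Aim 3 has a related but smaller problem. The hypothesis speaks of prevalence in controls, while the described prevalence estimator stops at the athlete sample. A reader could take a later questionnaire-based contrast for a contrast in diagnosed ED.

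**Working it through.** **1. The plan's own interview numbers.** Sample size calculation gives 43 men + 43 women = 86 athletes, then about 30 in each of three discipline groups, 3 × 30 = 90. The 43 can be approximated with the Wald z-test for logistic regression, taking a standard normal predictor (an assumption), P0 = 0.30, OR = 4, R² of other covariates = 0.20, power 0.80 and one-sided alpha 0.05:

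n = (z₀.₉₅ + z₀.₈₀)² × v / (ln 4)² / (1 − 0.20)

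Here v = 10.36 is the unit variance of the slope from the information matrix. So n = (1.645 + 0.842)² × 10.36 / 1.922 / 0.80 = 41.7, that is 42 against the stated 43. The article does not state sidedness; two-sided gives 52.9. Nothing below depends on this. What matters is that the whole interview allocation is to athletes.

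**2. Reference results available.**

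| Group | Planned n | Interviews | AUC against interview |
|---|---|---|---|
| Athletes | 300 | about 90 | estimable |
| Controls | about 300 | 0 | undefined |

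With no cases and no non-cases established, neither sensitivity nor specificity has a denominator in controls. A larger control group does not help.

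**3. Is another reference named for controls?** None is. Self-reported previous ED diagnoses are collected, but as health data and not as a reference. The EDE-Q and BEDA-Q are assigned to convergent validity of the EAT-26. The article also reports item overlap between instruments, with one item common to the EAT-26, BEDA-Q and EDI-3.

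**4. Which routes to prevalence reach controls?**

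| Route | Athletes | Controls |
|---|---|---|
| Diagnosed cases | yes | no interview |
| Mean predicted probability | yes | outside the stated sample |
| ED instruments | yes | EAT-26 at T0, T2, T3; EDE-Q at T1 |

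The third route is open. As an illustration, assume 20% of athletes and 10% of controls score above a cut-off. With 300 per group, the pooled rate is 0.15, the SE under the null is √(0.15 × 0.85 × 2/300) = 0.0292 and the SE under the alternative is √(0.16/300 + 0.09/300) = 0.0289. Power is Φ((0.10 − 1.96 × 0.0292)/0.0289) ≈ 0.93. The hypothesis concerns weight-sensitive sports only, about 100 ballet + 100 bodybuilding = 200. For 200 against 300 the pooled rate is 0.14, the SEs are 0.0317 and 0.0332, and power is Φ((0.10 − 1.96 × 0.0317)/0.0332) ≈ 0.87. With 15% in controls, power at 300 per group falls to about 0.36. These rates are assumptions; the article gives none for controls.

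**5. Would interviewing some controls rescue the ROC comparison?** Assume AUC 0.80 in both groups, 27 cases among 90 athletes (30%), and ED prevalence of 2% to 10% in controls. The Hanley-McNeil variance is [A(1−A) + (n₁−1)(Q₁−A²) + (n₀−1)(Q₂−A²)]/(n₁n₀), with n₁ cases, n₀ non-cases, Q₁ = A/(2−A) and Q₂ = 2A²/(1+A). The athlete SE is 0.056. The 95% half-width of the AUC difference is 1.96 × √(SE² athletes + SE² controls).

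| Control interviews | Cases at 2% to 10% | Control SE | Half-width of difference |
|---|---|---|---|
| 90 | 2 to 9 | 0.190 to 0.091 | 0.39 to 0.21 |
| 300 | 6 to 30 | 0.109 to 0.050 | 0.24 to 0.15 |

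Under these assumptions even 300 control interviews would leave the difference uncertain by about 0.15 or more.

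**The case against.** The strongest reply is that the damage is narrow, and much of it stands.

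- *A reader might infer that the prevalence comparison with controls cannot be made at all.* The documents do not support that. Objectives names ED instruments as a second source, and controls complete the EAT-26 and EDE-Q. Only the diagnosis-based and model-based versions are closed.
- *A reader might infer that the methodological aim fails.* It does not. That aim asks whether conventional instruments measure symptoms differently in the two groups, and the multi-group CFA, planned first, needs no ED status.
- *A reader might infer that any questionnaire-based AUC in controls is circular.* That goes too far. A single reference common to both groups, sharing no items with the index test, would be imperfect but not circular.
- *A reader might infer that missing sport-specific scales keep the prevalence model from controls.* Controls do lack the weight-pressure and ART scales, but the selected predictors could equally be ones they complete. What excludes controls is the stated restriction to the athlete sample.

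The full protocol could name a common reference. As published, however, the ROC sentence conflicts with five statements on who is interviewed, and nothing in the article reconciles them.

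**Conclusion.** The athlete-versus-control ROC comparison cannot be carried out against the stated reference test: 0 of about 300 controls have a result. This follows from the design alone and rests on no assumption about effect size, prevalence or sample size. The assumed rates and AUC above serve only as illustrations.

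For aim 3 the finding is one of labelling and interpretation. The control contrast can be computed, but it compares self-report results and not diagnosed ED. The EAT-26 cut-off of 12.66 is given for athletes, so applying it to controls leans on the very equivalence that the invariance analysis is meant to test.

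The primary objective, aim 2 and the comparison of weight-sensitive with less weight-sensitive sports do not depend on control interviews. This should be fixed, but it does not threaten the study's main results.

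**What to change.** 1. **ROC comparison.** Delete it, and answer the methodological aim with the planned multi-group CFA; item-level DIF may be added. If a comparison is kept, name in advance one self-report reference collected identically in both groups and free of items shared with the index test. Report the result as agreement with a self-report measure, not as diagnostic accuracy for ED. The EDE-Q at T1 is a candidate, subject to an item-overlap check and to its timing about a month after the baseline EAT-26. The BEDA-Q shares at least one item with the EAT-26. The text also limits a third instrument to athletes while Table 1 marks the BEDA-Q for both groups; that should be reconciled.
2. **Aim 3.** State that the contrast with controls is instrument-based. Report screen-positive rates or scores, avoid the term ED prevalence for it, and interpret it in light of the invariance results.
3. **Registration.** Update the register entry if it carries the same analysis.

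The cost is a wording change and one secondary analysis dropped or relabelled. No new data are needed.

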### Sample size calculation

Sample size planning is based on the statistical verification of the primary objective. To estimate the required sample size, we conducted an a-priori power analysis using G*Power 3.1.9.7 [90]. We expect weight pressure, internalisation of a sport-specific body image, unhealthy training attitudes and behaviours, and physical and psychological fatigue symptoms to predict DE in athletes [16]. To assess the validity of the model, a hierarchical regression model will be computed for men and women respectively. Thus, the number of predictors tested will be six, and total predictors of the regression model include nine predictors with sociodemographic data. Effect sizes for men athletes were found to be smaller than for women athletes [91]. However, the strive for muscularity is not considered in most studies investigating DE in athletes, which has been described as a promising indicator to explain variance in ED symptomatology especially in men [92]. Consequently, effect size for men and women athletes are expected to be medium (Cohen’s *f*^2^ = 0.15) in the present study [3, 93]. The power for the sample size calculation was determined to 1-*ß* = 0.95. This results in a sample size of *n* = 146 for men and women athletes for the quantitative data assessment, respectively. Sample size per sports discipline (ballet, bodybuilding, and ball sports) will be balanced with approximately *n* = 100 each (total *n* = 300). For the comparison with the control group, *n* = 300 control participants are also sought.

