To identify risk or protective factors affecting DE over time as stated in *further aims*, among others linear-mixed models will be conducted. These models assume that data are missing at random (MAR). Attrition bias will be evaluated by comparing baseline characteristics between participants with complete and incomplete follow-up data. If systematic differences are observed, sensitivity analyses will be considered to assess the robustness of the findings.

Exploratory analysis may include interaction testing, pathway analysis (e.g., structural equation modelling), latent class models, or network analysis to examine complex relationships among predictors and ED symptoms. If systematic differences are observed between athletes participating in the clinical interviews and those participating in surveys only, inverse probability weighting may be applied as a sensitivity analysis to account for potential selection bias by weighting individuals according to their estimated probability of interview participation. If substantial overlap between related constructs is detected, sensitivity analyses using alternative operationalisations (e.g., separate versus composite predictors) will be conducted to evaluate model stability and robustness. Sensitivity– and subgroup analyses may additionally examine models combining clinically diagnosed EDs and subclinical DE presentations. Potential sex differences among athletes in the factor structure of ED instruments will be assessed through a measurement invariance analysis.

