Many studies recruit athletes from various sports disciplines and generalise their results across all elite sports [102], instead of considering sports discipline-specific demands [103]. The focus on distinct sports disciplines permits nuanced analysis of differences in ED psychopathology among those disciplines, and particularly in relation to weight sensitivity, while at the same time reducing generalisability across the broader spectrum of elite sports.

However, methodological challenges remain. Research in elite sports is constrained by a highly selective group with limited availability due to demanding training schedules. This often results in small sample sizes, which reduces statistical power and hinders the detection of small but potentially meaningful effects [104, 105]. To maximize sample size and utilize validated instruments, the online assessments are conducted in English. However, including non-native English speakers may introduce bias due to potential comprehension difficulties and reduce generalisability. To monitor this, participants are asked to report their nationality. Additionally, participant drop-out across the four measurement points is a concern; to mitigate this, reminder notifications will be sent and an expense allowance will be provided. Framing eating behaviour as the primary research focus and the employed recruitment strategies may introduce self-selection bias, attracting athletes who are either currently experiencing DE or are entirely unaffected, thereby limiting the sample’s representativeness. As participants must be informed about the study’s content, this limitation cannot be fully avoided. To mitigate bias, recruitment materials deliberately avoided the term ED and instead referred to eating behaviour, thus better reflecting the study’s broader scope beyond clinical DE. Voluntary participation in clinical interviews improves feasibility but may again attract those with greater symptom burden.

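### For the longitudinal further aims, sensitivity analysis for drop-out hinges on a baseline comparison that cannot tell MAR from MNAR

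*Protocol article*

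**What the plan says.** The rule is in the protocol article, Planned data analysis. The mixed models are introduced for the further aims ("To identify risk or protective factors affecting DE over time as stated in" those aims) and are stated to assume MAR. Two sentences then deal with drop-out. The first gives the check: "Attrition bias will be evaluated by comparing baseline characteristics between participants with complete and incomplete follow-up data". The second gives the consequence: "If systematic differences are observed, sensitivity analyses will be considered to assess the robustness of the findings".

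No other check on drop-out appears in the article. The inverse probability weighting mentioned in the same section concerns which athletes take part in the clinical interview, not who is lost to follow-up. The Discussion acknowledges that "participant drop-out across the four measurement points is a concern" and answers it with reminders and an expense allowance.

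On timing, contact details are "used to contact participants one, six and twelve months after baseline assessment for follow-up assessments" (Participant eligibility and recruitment), and "The EAT-26 is administered at T0, T2 and T3 and is used as a measure of ED symptom severity" (Outcome measures). EAT-26 is therefore seen at 0, 6 and 12 months. Table 1 also schedules BEDA-Q, PHQ-4, perceived exertion and rating of fatigue at every wave, and EDE-Q at T1.

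**The concern.** A mixed model under MAR tolerates drop-out that depends on anything observed and in the model, including the baseline outcome. What it does not tolerate is drop-out that depends on values it never sees. Comparing baseline characteristics shows whether drop-out is related to baseline, that is, whether data are missing completely at random. It does not bear on the assumption the article states one sentence earlier. Yet it decides whether robustness is examined at all.

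A quiet baseline comparison would then be read as evidence against attrition bias, which it is not. A positive one may prompt sensitivity work where the model is already adequate. At stake are the 12-month conclusions, mainly mean change and comparisons of change between groups that lose participants for different reasons. Unrecorded worsening is plausible with EAT-26 six months apart. In addition, interviewed athletes found to have an eating disorder are offered counselling and treatment after baseline, and controls are not interviewed.

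**Working it through.** The article gives no figure for drop-out or attrition bias, so there is nothing of its own to reproduce. The check is a simulation of the rule.

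**Inputs from the article.** 300 athletes and 300 controls (Sample size calculation); EAT-26 at T0, T2 and T3; significance at 0.05 (Planned data analysis).

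**Assumptions.** About 30% lost by T3; the strength of dependence; the covariances. Systematic difference is taken as a t-test at p < 0.05 between complete and incomplete cases. All values are in baseline SD units.

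**Check 1: two time points.** T3 = T0 + change, SD of change 0.77, true mean change 0.
- Drop-out: logit(p) = −0.95 + 0.8 × s, where s is either standardised change (unseen) or T0 (seen).
- MAR estimate: regress T3 on T0 in completers and average the prediction over everyone. With monotone loss this matches the likelihood-based model.

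| Drop-out depends on | Baseline EAT-26 comparison fires | Bias in mean T3 |
|---|---|---|
| worsening, unseen | 5% | −0.17 SD |
| T0 severity | 100% | 0.00 SD |

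The 5% is simply the test's false-positive rate.

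**Check 2: three time points.** 300 athletes, 4,000 runs, about 30% drop-out, log-odds 1 per SD, a likelihood-based repeated-measures model on T0, T2 and T3, true mean change 0. The model contains a baseline indicator whose true effect on change is 0.20. A further baseline variable is left out of the model.

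| Drop-out depends on | Fires, baseline EAT-26 | Fires, any of 3 baseline variables | Mean change | Indicator effect |
|---|---|---|---|---|
| A. baseline EAT-26 | 100% | 100% | 0.001 | 0.201 |
| B. unseen worsening unrelated to baseline | 5% | 14% | −0.161 | 0.201 |
| B2. unseen worsening partly predicted by the indicator | 8% | 35% | −0.157 | 0.182 |
| C. worsening already recorded at T2 | 5% | 15% | 0.000 | 0.200 |
| D. the omitted baseline variable, which also drives change | 5% | 100% | −0.118 | 0.198 |

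The empirical standard error of mean change is 0.06 to 0.07. In A the rule fires with no bias. In B and B2 it is usually silent with bias. In C it is usually silent and silence is harmless. In D it fires and is right to.

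**Check 3: athlete-control contrast.** Set-up of check 1 with 300 per group and no true difference in change. Athletes drop out on unseen worsening at 0.8 per SD.

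| Log-odds in controls | Bias of contrast | Falsely significant |
|---|---|---|
| 0 | −0.167 SD | 63% |
| 0.4 | −0.081 SD | 21% |
| 0.8 | 0.00 SD | 5% |

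The athletes' baseline EAT-26 comparison fires in about 4 to 6% of runs throughout. Athletes would appear to fare better than controls when they do not. With the same mechanism in both groups the bias cancels.

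**The case against.** Several stronger readings are tempting, and the documents do not support them.

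- **That any drop-out following post-baseline worsening biases the models.** It does not. EAT-26 at T2 is itself an outcome in the model, so loss after a worsening recorded at T2 is still MAR (scenario C). Where loss occurs after T2, including T2 roughly halves the bias from unseen worsening (−0.165 to −0.087 SD).
- **That the baseline comparison is useless, or fires only when the model is valid.** Scenario D shows the opposite for a baseline variable omitted from the model. The article compares baseline characteristics in general, so the 5% for EAT-26 alone understates how often some difference would be seen: 35% over three variables in B2.
- **That the risk-factor findings are badly biased.** The stated purpose of the models is to identify such factors. For a continuous indicator the coefficient moves from 0.20 to 0.18 against a standard error of about 0.05, and a null indicator stays null. The bias falls on mean change and on group contrasts.
- **That the primary objective is affected.** The rule governs only the further aims. The hierarchical and logistic regressions have their own complete-case rule.

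It can also be said that a journal article may leave the form of a sensitivity analysis to the analysis plan. That is fair for delta steps and imputation details, and a statement that analyses will be considered does not forbid others. It does not cover the trigger, which the article itself states and which rests on the wrong evidence.

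**Conclusion.** The point holds in a limited form. The article conditions sensitivity analysis for drop-out on a comparison that cannot address the assumption its mixed models need. The size depends on an assumed 30% drop-out and on the assumed strength of dependence on unrecorded worsening. At log-odds 0.8 per SD, mean T3 severity is about 0.17 SD too low with the baseline EAT-26 comparison at its false-positive rate. An athlete-control contrast is off by 0.08 to 0.17 SD when the mechanism differs between groups, and by nothing when it is the same. No data on actual drop-out are available, so these are illustrations of what the rule can miss, not forecasts. Because only the further aims are concerned, the weight is moderate: the wording should be changed, but nothing in the primary analysis or sample size depends on it.

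**What to change.** 1. Remove the condition. Keep the baseline comparison as a description of who was lost, and put baseline predictors of drop-out into the mixed model, which deals with scenario D.
2. Also compare last observed post-baseline scores by the wave at which participants were lost and by group, rather than complete versus incomplete, which pools someone lost after T0 with someone who missed one wave. PHQ-4 is scheduled for both groups at every wave. BEDA-Q and EAT-26 can be added where available. Whether controls complete BEDA-Q should be settled first, since Table 1 lists it for them while Outcome measures describes a third instrument for athletes only.
3. Use these scores as auxiliary variables, for example by multiple imputation before the mixed model, so that MAR is more plausible.
4. Always report one sensitivity analysis under departures from MAR, for example a delta-adjusted analysis in which missing T2 and T3 EAT-26 values are worsened in steps, separately for athletes and controls.

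The cost is a change of wording and a few extra models on data already scheduled for collection.
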